## Methods/design

### Participants

Participants will be 176 individuals, aged 18–55 years, with a Body Mass Index (BMI) ≥30.0 kg/m^2^ who can provide informed consent, have sufficient English skills, and are able to attend treatment on campus. Participants are excluded if they have been diagnosed with somatic conditions (e.g. neurological disorders, stroke, head injury); serious psychiatric/psychosomatic conditions (e.g. psychotic disorder, suicidality, severe substance use disorder, developmental or intellectual disability); impediment in hearing, vision, or language with an effect on testing; previous or planned bariatric surgery; use of medication that impacts weight or executive functioning (e.g. antipsychotics, sedatives). These inclusion and exclusion criteria will allow for recruitment of a representative study sample, heterogeneous with regard to body weight, degree of obesity, and prevalence of typical comorbidities.

### Procedure

Participants will be recruited from clinic settings and the community, with close to equal numbers of male and female subjects (although more female subjects are anticipated based on previous trials). Advertising will also be placed on social media sites, community notice boards and newspapers. Participants will be asked to provide their contact details if they are interested in taking part in the study. The research psychologist will telephone or email the participant to make contact and to inform them about what is involved. If the participant is interested in taking part, the psychologist will conduct a screening interview to assess whether the potential participant is suitable and will schedule an assessment time.

This is a double-blind study; participants are blind to the design of the study, i.e. they are not provided with any information regarding the CRT-O intervention prior to randomisation and research assistants are blind to the participants’ group allocation at post-treatment and follow-up assessments. Participants are informed that two different weight-loss treatments are being compared. Participants will be required to have a GP who is responsible for their medical management during the trial. Participants will be randomly assigned to one of two groups using computer-generated random numbers, provided in a document developed by a researcher not in charge of recruitment or assessment:BWL alone group = 8 sessions of individual BWL plus 12 sessions of group BWL orCRT-O + BWL group = 8 sessions of individual CRT-O plus 12 sessions of group BWL

The RCT has been registered with the Australian New Zealand Registry of Clinical Trial (trial id: ACTRN12616000658415). The trial followed the SPIRIT guidelines (see additional file 1).

### Behavioural weight-loss intervention (BWL)

Those in the BWL group will attend eight individual sessions with a psychologist, where they will receive extensive education about weight-loss techniques and receive support towards achieving their weight-loss goals including managing emotions, cravings and establishing hunger cues. Following this, they will attend 12 weekly (2-h) BWL group sessions which will teach them how to change their diet and exercise habits to enable weight loss. Treatment requires participants to record their diet and exercise behaviour in a diary.

During these sessions the psychologist will reinforce the BWL strategies and help the participant to problem-solve any difficulties that they are having with their implementation. The group programme is a modified version of the Look Ahead trial [18, 19]. The Look Ahead trial is an intensive lifestyle intervention programme that targets diet and exercise through behavioural modification techniques and has been extensively researched [18, 19]. The programme has been modified to include Australian dietary and physical activity guidelines. Interestingly, BWL programmes have been found to be more successful at enhancing weight loss than cognitive behavioural therapy [20].

During BWL, behavioural techniques are used to help participants modify eating and exercise habits. A dietitian will conduct an early BWL group session regarding dietary advice. Participants are taught to manipulate their environment at home and at work by limiting cues associated with eating and increasing cues associated with exercise. For example, participants are encouraged to keep high-fat, high-calorie foods out of their house and work area. Problem-solving techniques are taught so that participants can effectively deal with difficult situations that threaten their weight-control efforts. Thoughts and emotions related to overeating and inactivity are also addressed during treatment sessions to understand and decrease the influence of these factors on weight control. Stress management, craving exposure and mindful eating techniques will be taught and attention is given to motivation enhancement and relapse prevention to help individuals to maintain their weight loss. Homework will also be provided.

### Cognitive Remediation Therapy for Obesity (CRT-O)

CRT-O is a manualised intervention that consists of mental exercises aimed at improving executive function via practice [14]. CRT promotes reflection on thinking styles, develops metacognition and helps to explore and apply new thinking strategies in everyday life. The primary function of CRT is to improve the thinking process rather than the content [21–23]. A manual was developed for the pilot CRT-O trial. The current trial will also utilise this manual. The CRT-O treatment will be delivered face-to-face by two clinical psychologists. The main components and principles of CRT-O are based on the original CRT-AN treatment. However, some important modifications have been made to adapt the manual for obesity and these are described in Smith et al. [14]. Homework will also be provided.

### Assessment

Participants will complete a comprehensive assessment at baseline, at post-treatment and 1-year follow-ups consisting of:
*Demographics*: age, sex, ethnicity/race, socioeconomic status (by postcode, income, education), and language use
*Anthropometric measures*: we will measure: (1) height and weight with calibrated scales (to derive BMI in kg/m^2^), (2) hip and waist circumferences to calculate the waist to hip ratio, and (3) we will use a portable bioelectrical impedance scale (from Tanita) to calculate an estimate of total body water, which can then be used to estimate fat-free body mass and, by difference with body weight, body fat. (One study showed that Tanita and DEXA measures correlated at 0.96 [24]). Weight will be measured at every session
*Exercise*: participants will wear an accelerometer for 1 week (at three time points) to assess physical activity levels. Accelerometers are effective tools that continuously record physical activity over specified time intervals. The data output also allows for an estimate of physical activity intensity and energy expenditure (which are not possible with alternative methods, such as pedometers). To not over-burden participants during assessment (week 0), the accelerometer will be provided in week 1 of the intervention
*Neuropsychological assessment*: a targeted assessment of cognitive function will be completed at the time of their preference. It will include:
*Executive function:* the *Wisconsin Card Sorting Test* (WCST)-64: the computerised version of the WCST [25, 26] will be used. In this test, subjects are instructed to categorise a series of cards according to one of three stimulus features (colour, shape or number), without this principle being revealed to the subject. After each association, the only feedback given is whether a match is correct or incorrect, the idea being that subjects should infer how to categorise based on the feedback they receive. This test measures categorisation, inference, testing of hypotheses, cognitive flexibility, cognitive inhibition and response to feedback [27]. The number of total errors and perseverative errors and failure to maintain a set are the dependent measures. The WCST is regarded as a valid measure of abstract reasoning ability to maintain and appropriate planning and problem-solving strategies across changing stimulus conditions to obtain a future goal; it is the most widely used test of executive function [28]
*Trail Making Test* (TMT) [29]: this will be used to assess psychomotor speed, visual integration, cognitive flexibility and inhibitory control. This test measures the subject’s ability to connect written numbers in an ascending order (Trail A), and, afterwards, to connect numbers and letters, alternating numbers in ascending order and letters in alphabetical order (Trail B), for example, 1-A-2-B. The score is the response time taken to complete the respective trails [28]
*Behaviour Rating Inventory of Executive Function* (BRIEF-A): participants will complete the BRIEF-A Self-report Form. This instrument is a 75-item standardised measure that records views of an adult’s executive functions or self-regulation in a person’s everyday environment. It has been shown to be a reliable and valid measure of executive functioning in individuals across a broad age range [30]
*Memory: Wechsler Memory Scale* (WMS), *Logical Memory Subtest*: the Logical Memory Test is the most widely used measure of memory [31], and it targets auditory-linguistic memory. The task demands verbal recall of spoken story passages
*Language: Boston Naming Test* (BNT): the BNT is a 60-item confrontation naming test which is considered to be a reliable measure of word retrieval performance [32]
*Nutrition*: a comprehensive assessment, using a 1-week food diary, will be conducted by a dietitian and will be analysed using FoodWorks software. The Foodworks Professional package includes food composition tables and contains nutrient values for more than 4200 foods, beverages and supplements. FoodWorks is suitable for dietary analysis and meal planning
*Inflammatory markers*: tumor necrosis factor-α (TNFα), interleukin-6 (IL-6), inflammasome-activated IL-1β and C-reactive protein will be measured
*Clinical assessment*: a brief clinical assessment will verify comorbidities such as an eating disorder, depression or anxiety. The participant will also be asked questions related to their previous weight-loss attempts and beliefs about weight loss. The following measures will also be completed:
*Depression, anxiety and stress*: will be measured by the 21-item *Depression, Anxiety and Stress Scale* (DASS) [33], a well-validated Australian measure. It has been validated in clinical and nonclinical populations and has good reliability [33, 36]. Research has indicated that individuals who are obese are at an increased risk of developing depression and depression has been found to be predictive of obesity [34]. Also, the association between depression and obesity has been found to have a dose-response gradient where the association between depression and obesity has been found to be stronger than that between depression and being overweight [35]. There is a significant evidence base that indicates that depressive disorders are associated with deficits in cognition, including difficulties with verbal learning and memory [37], attentional functions, executive control, lowered cognitive flexibility [38] and interpretation biases [39, 40]
*Eating disorder symptoms*: eating disorder symptoms are to be measured by the *Eating Disorder Examination Questionnaire* (EDE-Q) [41]. The EDE-Q has 36 items and measures concerns about shape, weight and eating; restraint and self-reported binge eating. Subscale scores for shape, weight and eating concerns and restraint range between 0 and 6. A higher score indicates more severe eating psychopathology. This has been validated in community samples in Australia and it has been shown to hold acceptable internal consistency and test-retest reliability [42]. The BED and purging subsections of the EDE will also be administered
*Grazing Questionnaire*: grazing refers to ‘uncontrolled, repetitive eating of small amounts of food’. Grazing has been implicated as an eating behaviour which is associated with obesity. This measure is a 9-item self-report questionnaire which asks specific questions regarding eating behaviour [43]
*Quality of Life*: this will be assessed using the *Short Form-12 Health Status Questionnaire* (SF-12). This is a well-known and validated measure of functional limitations associated with impairment in physical and mental health

### Treatment fidelity

The clinical psychologists delivering the treatment will be trained and regularly supervised. Therapist adherence will be monitored through audio-recordings and monthly supervision sessions. Adverse events assessed by the psychologists will be reported to the Ethics Committee immediately. A psychologist can refer a participant to another psychologist for treatment of mental illness at any time. In addition, randomly selected taped sessions of CRT and BWL will be reviewed by two of the project’s principal researchers who will apply a previously developed Treatment Adherence Measure to the taped sessions. The Work Alliance Inventory (WAI) will be administered during weeks 4 and 8 of individual treatment to assess therapeutic alliance. In weeks 4, 8 and 12 of group treatment, the Group Climate Scale (GCS) will be provided to assess group factors. Session attendance will also be recorded.

### Data collection and analysis

Data is collected at baseline, post treatment and at 1-year post-treatment follow-up. See Table 1 for assessment tests and times of data collection. The Statistical Package for Social Sciences (SPSS) statistics will be used to analyse data. Data entry will be done and checked by two research assistants and stored in the university’s server. The principal researchers will conduct the analyses for the main results with assistance of trained statisticians. The Data Monitoring Committee is comprised of two researchers, one with expertise in cognitive remediation therapy and the other is the primary researcher (ES).

**Table 1 Tab1:** Assessment tests and times of data collection for both groups

Assessments	Screening	Initial assessment (week 0)	Week 1 of treatment	Weeks 2–20 of treatment	Post treatment (week 20)	Follow-up (week 52)
Inclusion/exclusion criteria	X					
Demographic data		X			X	X
Anthropometric measures		X		X (at the end of one-to-one intervention)	X	X
Clinical assessment		X			X	X
Neuropsychological assessment		X			X	X
Nutrition data		X			X	X
Inflammatory markers		X			X	X
Accelerometers			X		X	X

#### Power calculations

We calculated the sample size with a method that takes into account the intracluster correlation coefficient (*r* = .02) for comparison between groups using a two-tailed linear mixed model, predicting a small effect size (Cohen’s *d* of 0.2) on weight loss and using a power of 80%, and determined that a sample size of 70 individuals per group is needed. Assuming an attrition rate of 25% per group, a sample of 88 per group is necessary, totalling 176 participants.

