## Discussion

If CRT-O (plus BWL) is successful at assisting people to lose weight and to maintain the weight loss it would allow for the development of an intervention that could significantly improve treatment outcomes. Given the poor long-term outcomes for previously investigated treatments (excepting bariatric surgery reserved for the most severe cases) and the increasing public health burden of obesity, novel and integrative treatment approaches are urgently needed.

Our RCT is designed to compare two groups, a CRT-O (plus BWL) group to a BWL alone group. We will investigate whether CRT-O (plus BWL) is effective in improving a person’s ability to lose weight, to maintain their weight loss and to improve their executive functioning, compared to BWL alone. The strengths of our design include its large sample size, the use of validated and standardised assessments, and its double-blind study design. We will also be the first to measure inflammatory markers to discern whether there is an association between inflammation, weight and executive function in obese individuals.

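### The stated inputs (d = 0.2, two-tailed, 80% power, ICC .02) do not give 70 per group: they need about 393 per group before clustering, and 70 per group gives about 22% power

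*Protocol article*

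**What the plan says.** The Power calculations section describes a sample size "for comparison between groups using a two-tailed linear mixed model" that allows for an intracluster correlation of .02. The assumed effect is given as "predicting a small effect size (Cohen’s *d* of 0.2) on weight loss". From these inputs the section concludes: "on weight loss and using a power of 80%, and determined that a sample size of 70 individuals per group is needed". It then raises 70 to 88 per group, 176 in total, for 25% attrition.

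The section gives no alpha, no cluster size, no number of repeated measurements and no within-person correlation. It does not say which standard deviation d is scaled on. The Abstract lists percentage weight loss among the primary outcomes, and Main analyses compares it between groups by linear mixed models. No other power statement appears in the article.

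**The concern.** By convention d = 0.2 is a small effect, and two-group comparisons at that size usually need several hundred people per arm. Seventy per arm is what one expects for an effect near 0.5. The intracluster correlation cannot explain the gap, because a positive correlation within therapy groups raises the required number.

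This is the only power figure for a primary outcome. If the true effect were 0.2, a non-significant result would be the likely one, at roughly four times in five. A reader told that the trial had 80% power at 0.2 could then take that result as evidence that the cognitive remediation component adds nothing.

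**Working it through.** **Inputs.** From Power calculations: d = 0.2, 80% power, two-tailed, ICC .02, 70 evaluable per group, 88 randomised per group, 25% attrition. Assumed: alpha .05 two-sided, and clusters of 5 to 20 people.

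**1. The plan's figure from its own inputs, before clustering.** n per group = 2(z₀.₉₇₅ + z₀.₈₀)²/d² = 2(1.960 + 0.842)²/0.2² = 15.70/0.04 = 392.4, so 393. The noncentral t gives 393.4. The stated 70 is not reproduced; the ratio is 393/70 = 5.6.

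**2. Looser alpha.** At .10 two-sided (the same as .05 one-sided), n is 310 per group, and power with 70 is 32%.

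**3. Clustering.** Design effect = 1 + (m − 1) × .02.

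| Cluster size m | Design effect | n per group for d = 0.2 | Power at d = 0.2, 70 per group | Power at d = 0.2, 66 per group | Detectable d at 80% power, 66 per group |
|---|---|---|---|---|---|
| none | 1.00 | 393 | 22% | 21% | 0.49 |
| 5 | 1.08 | 425 | 20% | 19% | 0.51 |
| 10 | 1.18 | 464 | 19% | 18% | 0.53 |
| 20 | 1.38 | 543 | 17% | 16% | 0.58 |

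The 66 is 88 × 0.75. With all 88 per group evaluable and no clustering, power at d = 0.2 is 26%.

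**4. Routes back to about 70.** Each was tried to see what the plan might have done.

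- *Averaging the two post-baseline visits.* The factor is (1 + ρ)/2. This gives 197 per group at ρ = 0 and 295 at ρ = 0.5.
- *Averaging 20 sessional weights.* The Assessment section says weight is taken at every session. With ρ = 0.5 the factor is (1 + 19 × 0.5)/20 = 0.525, giving 207 per group.
- *Reading .02 as a within-person correlation.* The factor is (1 + (m − 1) × .02)/m for m measurements. This gives 137 per group at three measurements, 105 at four and 73 at six. It comes close to 70 only at about six, and only if one person's repeated weights were almost unrelated.
- *d scaled on the SD of body weight.* A change score has factor 2(1 − r): 393 × 2 × (1 − 0.911) = 70. Baseline adjustment has factor (1 − r²): 393 × (1 − 0.907²) = 70. Both need a correlation near 0.91.
- *Group-by-time interaction at f = 0.1.* With four time points and ρ = 0.5 the total is 138 (69 per group). With three time points and ρ of about 0.57 it is 140. With ρ = .02 it is 318 (three time points) or 270 (four).
- *A medium effect.* d = 0.5 needs 63 per group; with a design effect of 1.10 that is 69.

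Every route that lands near 70 changes the effect size or its definition, gives the .02 another meaning, or adds a correlation the article does not state.

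**The case against.** The strongest reply is that the article names a linear mixed model, so a t-test with a design effect is only one reading of an under-specified calculation. Weight is recorded often, and Table 1 adds an anthropometric measurement at the end of the one-to-one phase. The section also says weight loss, not percentage weight loss. If d was scaled on the spread of body weight, a correlation near 0.91 between serial weights in the same adult may be realistic, although the documents give no figure. Repeated measures therefore cannot be ruled out as the source of 70.

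That stands, and it limits the point. It does not make the sentence correct. Such a calculation rests on unstated inputs, and its d would not be an effect of 0.2 standard deviations in percentage weight loss.

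A reader might infer that the trial cannot detect a benefit, or that a null result is to be expected. The documents do not support that. Power of about 20% applies only if the true effect is 0.2. With 66 per group and no clustering, power is 81% at d = 0.5 and above 99% at d = 0.8. The Background reports a large effect on weight in the previous trial, though against a no-treatment control, whereas this control is active.

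Nor must the Discussion's sentence "The strengths of our design include its large sample size" be struck out. The trial is larger than the previous one of 80 people, so that is a matter of wording.

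**Conclusion.** Wrong as written. The effect size, power and sample size in the Power calculations section cannot all hold on the inputs given. About 5.6 times as many participants per group would be needed before clustering, and more with it. Power for d = 0.2 is about one quarter of the figure claimed. With 66 evaluable per group, 80% power is reached for an effect of roughly half a standard deviation, not for a small one.

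The conclusion rests on alpha of .05 two-sided, on the .02 being a correlation between people in the same cluster, and on d being scaled on percentage weight loss, as the Abstract and Main analyses suggest. The clustered figures also rest on cluster sizes of 5 to 20. The .10 alternative for alpha does not rescue the figure. A different scale for d could, but the section would then have to say so.

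That 88 per group leaves 66 and not 70 after 25% attrition is a separate matter. It barely changes the power here (22% against 21%).

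**What to change.** Keep 176 participants and rewrite the Power calculations paragraph.

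1. Remove the claim of 80% power for d = 0.2 on weight loss.
2. State alpha, the standard deviation on which d is scaled, the cluster size, and the number of and correlation between repeated measurements if these entered the calculation.
3. Restate what the sample can detect in percentage weight loss. With 66 evaluable per group and alpha .05 two-sided, there is 80% power for d of about 0.49 without clustering and about 0.51 to 0.58 with ICC .02 and clusters of 5 to 20 (0.53 at 10). Power for d = 0.2 is about 20%. A rounded 80% power at 0.5 should not be used with clustering, because at a cluster size of 10 the power at 0.5 is 75%.
4. Commit to interpreting a non-significant result through its confidence interval, not as evidence of no effect. With 66 per group and no clustering, the 95% interval is about ±1.96 × √(2/66) = ±0.34 standard deviations, so even an estimate of zero would not exclude 0.2.

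If the 70 came from another calculation, the sponsor should report its actual effect definition and correlation instead of the current wording, and still give item 3.

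The cost is rewording only, with no added participants. The downside is that the stated detectable effect becomes less favourable.

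### The 25% attrition allowance is computed as 70 × 1.25 rather than 70 / 0.75, so 88 randomised per group leave 66, not the 70 the plan requires

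*Protocol article*

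**What the plan says.** The Power calculations section of the protocol article gives three linked figures.

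- The requirement: the authors "determined that a sample size of 70 individuals per group is needed", for 80% power in a two-tailed linear mixed model with an effect on weight loss of d = 0.2 and an intracluster correlation of 0.02.
- The allowance for dropout and the resulting size: "Assuming an attrition rate of 25% per group, a sample of 88 per group is necessary, totalling 176 participants".

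The total of 176 is repeated in the Methods/design paragraph of the Abstract and under Participants ("Participants will be 176 individuals"). The article gives no other attrition rate and no other way of inflating the sample.

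**The concern.** An attrition rate is a fraction of those who enter the trial. To end with a required number, that number is divided by the fraction retained. Multiplying it by one plus the rate always gives too few, because the loss is then taken from a larger base than the one used to compute the allowance. The stated 88 looks like the product of that shortcut. If so, the plan misses its own requirement under its own attrition assumption, and the 80% power attached to 70 per group is not what 176 participants would provide.

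**Working it through.** **Inputs, all from Power calculations:** 70 required per group, 25% attrition per group, 88 per group (176 in total) to be enrolled.

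**1. Reproduce the plan's figure.** Required × (1 + rate) = 70 × 1.25 = 87.5, rounded up to 88. Doubled, this is 176. Both stated figures are reproduced exactly.

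**2. Apply the plan's attrition to that figure.** Enrolled × (1 − rate) = 88 × 0.75 = 66 per group, or 132 in total. Shortfall: 70 − 66 = 4 per group, and 4 / 70 = 5.7%.

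**3. Inflate correctly.** Required / (1 − rate) = 70 / 0.75 = 93.3, rounded up to 94 per group, or 188 in total. Check: 94 × 0.75 = 70.5, whereas 93 × 0.75 = 69.75 falls just short. The difference from the plan is 94 − 88 = 6 per group, or 12 in total, which is too large to be rounding.

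**4. Attrition that 88 per group can bear.** 1 − 70 / 88 = 0.2045, so at most 20.5%.

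**5. Consequence for power (illustrative).** The article states no alpha and does not show its full method, so I assume a two-sided alpha of 0.05 and an independent two-group comparison without clustering.

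- By the normal approximation, the effect that 70 per group detects with 80% power is (1.960 + 0.842) × √(2/70) = 0.474.
- At that same effect, 66 per group give Φ(0.474 × √(66/2) − 1.960) = Φ(0.760), about 77.6%. The loss is about 2.4 points.
- Using the t distribution, the effect detectable at 80% power moves from d = 0.477 with 70 per group to d = 0.491 with 66.

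**6. What this does not settle.** The same simple formula needs 393 per group for d = 0.2, and 70 per group give about 22% power at that effect. How 70 was derived is a separate question. Step 5 takes 70 as given, solely to isolate the cost of the attrition error.

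**The case against.** The arithmetic leaves little to dispute. The case on the other side concerns how much it matters.

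- **The loss is small.** Four completers per group and about two points of power change no estimand, analysis or conclusion, and the 25% is only a planning guess. This stands as a statement about size. It does not make the figure right.
- **The mixed model uses partial data.** Main analyses specifies linear mixed models, and Assessment says weight is taken at every session, so people who leave can still contribute and the effective loss may be under four per group. This is fair in part. But Power calculations already bases the 70 on a linear mixed model and then adds attrition on top, so the plan itself counts dropouts as lost from the 70. The hypothesis in the Background also covers the 1-year follow-up, where a participant who has dropped out has no weight.
- **The larger problem is the base of 70.** This stands. A reader should not conclude that 94 per group would restore 80% power at d = 0.2; on a simple two-group comparison it would not. The attrition step is still wrong whatever the base, and the same shortcut applied to a revised base would again fall short.
- **The detectable effects rest on assumptions.** They do. The figures 0.477 and 0.491 are illustrative, because the article gives no alpha and too little of its method to compute values consistent with it.

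**Conclusion.** The figure is wrong as written. The stated 70, 25% and 88 cannot all hold: 25% attrition from 88 leaves 66, and keeping 70 needs 94 per group (188 in total). This part follows from the plan's own numbers and needs no outside assumption.

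The practical consequence is modest: 12 participants in total, or about 2.4 points of power if 70 per group is taken to give 80%. That last figure assumes a two-sided alpha of 0.05, a simple comparison without clustering, and no contribution from participants who drop out. The case for correcting it is that 176 is the trial's headline size and this is its only justification in the article, rather than that the error threatens the trial's validity.

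**What to change.** Correct the attrition sentence in Power calculations in one of three ways.

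1. Keep 176 and 25%, and state that 88 per group leave 66 analysable per group. Give the matching detectable effect, computed by the sponsor's own method with alpha and the correlation assumptions stated.
2. Keep 176 and 70, and state that this tolerates attrition of about 20% (88 × 0.80 = 70.4). This should be chosen only if a rate of 20% can be supported, and not merely to fit the number.
3. Keep both 70 and 25%, and raise the target to 94 per group, 188 in total. The 176 in the Abstract and under Participants would then change as well.

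The first two cost a sentence and no participants, apart from rerunning the calculation in the first. The third costs 12 more participants. None should be presented as securing 80% power at d = 0.2 until the derivation of 70 has been checked. If that base is revised, the new figure should be divided by 0.75 rather than multiplied by 1.25.
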